### Outcomes

The primary outcome measure is the proportion of indexes with at least one partner who returns to the study site for partner services within 28 days of index diagnosis. Each PN slip will also have a unique ID that links partners to the index client, thus allowing for recording of this data. The main secondary outcome will be the number of days between index case diagnosis and the partner attending for partner services. Additional secondary outcomes will include uptake of PN slips by pregnant women, adverse birth outcomes in index cases, number of partners who receive treatment, and intervention cost. Number of partners who receive treatment will be recorded from our study antibiotic administration records, and compared with that reported by participants during telephone follow-up.

Furthermore, the proportion of indexes with at least one partner who returns to the study site for partner services any number of days from index diagnosis, will also be measured as a secondary outcome.

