### Main study procedures

The procedures for the main IPSAZ study are described in detail in the main study protocol
^
24
^. In summary, in addition to HIV and syphilis testing provided as part of routine care, the IPSAZ study will provide on-site opt-out testing for chlamydia and gonorrhoea using Xpert® CT/NG assay (Cepheid), for trichomoniasis using OSOM® Trichomonas Rapid Test (Sekisui Diagnostics), and for Hepatitis B using the HBsAg 2 (Abbott Diagnostics Medical Co. Ltd). Comprehensive case management, including treatment and partner notification, will be provided as per national guidelines
^
7
^, ideally on the same day as sample collection. For participants unable to be treated on the same day, they will be contacted by telephone up to five times over 28 days, to advise them to return for treatment. For participants with symptoms, participants will be given the option to receive immediate syndromic treatment, or to receive tailored treatment following processing of their results.

All pregnant women will be contacted by telephone after birth, to collect data on birth outcomes. Alongside this, they will be asked if they notified their partners, if their partners were treated, and if there were any negative consequences of this, including verbal, physical, sexual, or other abuse, relationship breakdown, negative reactions from friends or other family members, or any other ramifications.

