### Proposed intervention

As per standard of care, partners will be notified by client referral. Post-test counselling to participants diagnosed with an STI or treated for a syndrome will include the importance of partner treatment. They will be provided with PN slips for their partners to return for presumptive treatment. Index cases can receive as many PN slips as they require. Partners who attend the study clinic and present their PN slip will be provided with presumptive treatment free-of-charge. Partners will be considered lost-to-follow up if they have not returned within 28 days after treatment of the index case.

The intervention will be provision of $3 (USD) provided to a partner on returning to the clinic for treatment. The amount was based on in-depth interviews with pregnant women, male partners, and midwives, recruited when attending or working at one of the intervention clinics, as well as discussions with members of the intervention team. Questions on appropriate incentive value were embedded within broader discussions about PN, including different methods of PN, associated challenges, and feasibility of PN. Specifically for incentives, stakeholders were asked what they thought about the idea, any potential negative consequences, and what a suitable value would be for an incentive. Male partners often noted that an incentive should cover cost of travel, but also leave the partner with some additional money to spend. In contrast, pregnant woman and midwives tended to say any financial incentive, even very small, would prompt partners to attend. They also noted that unintended consequences could include using the incentive for alcohol or drugs, or for individuals who were not the index’s real partner to attend. A compromise value of $3 was therefore chosen, with a key factor being that $3 covers a return journey by public transport from the majority of locations from where pregnant women (and therefore potentially their partners) are likely to travel.

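### The primary outcome runs 28 days from index diagnosis while partner follow-up runs 28 days from index treatment, so some partners still in follow-up are scored as non-returns

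*Protocol article*

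**What the plan says.** All references are to the protocol article.

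- **Outcomes.** The primary outcome is the proportion of index women for whom one or more partners come back to the clinic "within 28 days of index diagnosis". The same section adds a secondary outcome without a time limit: return for "partner services any number of days from index diagnosis, will also be measured as a secondary outcome". The main secondary outcome, days to partner attendance, also starts at diagnosis.
- **Proposed intervention.** Follow-up has a different start: "Partners will be considered lost-to-follow up if they have not returned within 28 days after treatment of the index case". On the slips, this section says, after describing post-test counselling: "They will be provided with PN slips for their partners to return for presumptive treatment". The women concerned are those diagnosed with an STI and those treated for a syndrome.
- **Main study procedures.** Case management, including treatment and partner notification, takes place "ideally on the same day as sample collection". There is a plan for the rest: "For participants unable to be treated on the same day, they will be contacted by telephone up to five times over 28 days". Symptomatic women may take syndromic treatment at once, before results.
- **Statistical analysis.** The numerator is women given a slip for whom at least one partner came back, with no window. The denominator is all women given a slip.

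**The concern.** The same event, a partner's return, is timed from two different start dates, and the section that defines the estimate gives no window. The protocol itself expects some women to be treated after the day of testing, so the two dates will not always coincide. Where they differ, a partner can be under follow-up and already scored as a non-return.

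If the slip is handed over with treatment, late-treated women also have less than 28 days in which a return can count, and the shortfall equals the treatment delay. The endpoint would then partly measure how quickly the index woman was treated, as well as how partners respond to the slip.

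The start date also fits the analysis population imperfectly. A woman treated for a syndrome receives a slip and enters the denominator, but she may have no test-based diagnosis date, or one later than her treatment.

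At stake are the observed rates in both arms, some power in a trial not sized for this question, and the room left to choose between readings once data are in.

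**Working it through.** **1. The plan's own figure.** Inputs from Sample size calculations: 30% in the control arm, odds ratio 1.96, alpha 0.05 (sidedness not stated; two-sided reproduces), ICC 0, and 100 clusters × 1.5 = 150 women per arm.

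- Incentive-arm proportion: 0.30 × 1.96 / (0.70 + 0.30 × 1.96) = 0.588 / 1.288 = 0.4565.
- Power for two proportions with pooled variance under the null, 150 per arm: 80.1%.
- Solving for 80% power gives an odds ratio of 1.958 (stated 1.96). Dividing 150 by the design effect 1 + (1.5 − 1) × 0.1 = 1.05 gives 1.990 (stated 1.99).

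All 20 cells of Table 1 reproduce to within 0.01. The calculation is sound, but the 30% carries no time window either.

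**2. The dates.** Let L be the days from diagnosis to treatment. The primary window closes on day 28 from diagnosis and follow-up closes on day 28 + L. The primary window left after treatment is 28 − L.

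| L | Primary window left after treatment | Follow-up ends (days from diagnosis) |
|---|---|---|
| 0 | 28 | 28 |
| 7 | 21 | 35 |
| 14 | 14 | 42 |
| 21 | 7 | 49 |
| 28 | 0 | 56 |

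Example: a woman is treated on day 20 and her partner returns on day 35. That is 35 − 20 = 15 days after treatment, so he is within follow-up. It is also past day 28 from diagnosis, so the primary outcome is not met. A partner who returns by day 28 from diagnosis counts under either clock, however late the treatment.

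**3. Size, on assumptions.** The documents give neither the share of women treated late nor the timing of returns. Assume:

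- a share f is treated L days late, the same in both arms;
- the slip is issued with treatment;
- return times after treatment are exponential with mean m of 7 or 14 days, the same in both arms;
- 28-day-from-treatment rates are 30% and 45.7%.

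Formulas:

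- Share of a late-treated woman's 28-day returns that still count: c = (1 − e^(−(28−L)/m)) / (1 − e^(−28/m)).
- Multiplier on both arm rates: s = 1 − f + f·c.
- Women rescored as failures among 300: 150 × (0.30 + 0.4565) × (1 − s).

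Worked case, f = 20%, L = 21, m = 14: c = (1 − e^(−0.5)) / (1 − e^(−2)) = 0.393 / 0.865 = 0.455. Then s = 0.8 + 0.2 × 0.455 = 0.891. Rates are 0.30 × 0.891 = 0.267 and 0.4565 × 0.891 = 0.407. Rescored: 150 × 0.7565 × 0.109 = 12.4.

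| f | L | m | c | Rates | Odds ratio | Power | Rescored of 300 |
|---|---|---|---|---|---|---|---|
| 10% | 14 | 7 | 0.881 | 29.6%, 45.1% | 1.95 | 79.4% | 1.4 |
| 10% | 14 | 14 | 0.731 | 29.2%, 44.4% | 1.94 | 78.4% | 3.1 |
| 20% | 21 | 7 | 0.644 | 27.9%, 42.4% | 1.91 | 75.3% | 8.1 |
| 20% | 21 | 14 | 0.455 | 26.7%, 40.7% | 1.88 | 72.6% | 12.4 |
| 30% | 28 | either | 0 | 21.0%, 32.0% | 1.77 | 57.6% | 34.0 |

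The last row is an extreme. With L = 0 there is no effect. Because s multiplies both arms, the ratio of the two rates is unchanged, while the odds ratio and the absolute difference shrink.

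**The case against.** The strongest reply is that the primary outcome has one explicit clock. The Outcomes section states it, and both time-related secondary outcomes use the same anchor. The lost-to-follow-up sentence sits in the description of the intervention and can be read as an operational label. An outcome window shorter than follow-up is not in itself an error. The any-time secondary outcome picks up the late returns and would show how much the cutoff matters. Testing is on site and same-day management is the aim, so few women may be affected.

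Much of this stands, and it rules out several stronger readings:

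- *That late-treated women's partners are generally scored as failures.* Only those returning after day 28 from diagnosis are.
- *That a slip issued near day 28 can hardly succeed, so that exposure runs from 0 to 28 days.* This needs the slip to come with treatment. The text links slips to post-test counselling. For a woman who left before her result, issue on her return is a reasonable inference, but it is not stated.
- *That treatment may come up to 28 days after diagnosis and no later.* The 28 days are a period of telephone recall. The text sets no treatment limit and does not count those days from diagnosis. Nor is diagnosis defined: if it means the day the woman is told her result, the gap shrinks.
- *That the comparison is biased towards one arm.* Nothing in the documents suggests that treatment delay differs by arm.

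One part does not stand. The any-time outcome has no common window and leaves the primary definition as it is. Nothing in the text reconciles the two start dates or supplies the window missing from the Statistical analysis section.

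**Conclusion.** The inconsistency is certain on the text: two start dates for one event, and a numerator with no window. The harm is conditional. The expected effect is lower observed rates in both arms, modest attenuation of the odds ratio and some lost power, without clear directional bias. If 10% to 20% of women are treated two to three weeks late, roughly 1 to 12 of 300 women are rescored, the odds ratio moves from 1.96 to between 1.88 and 1.95, and power falls to about 73% to 79%. A serious loss (58%) needs 30% of women treated a full 28 days late. If treatment is same-day, the effect is nil.

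These figures rest on the assumed late share and delay, exponential return times, slip issue with treatment, and the same delay and return-time pattern in both arms. If the incentive also brings partners back sooner, the incentive arm would lose fewer returns and the attenuation could be smaller or reversed. The documents do not settle this.

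This should be fixed, because it concerns the definition of the primary endpoint and the choice between readings should be closed before analysis. It does not invalidate the design or the sample size figures.

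**What to change.** Before analysis, reconcile the Proposed intervention, Outcomes and Statistical analysis sections on one start event and one 28-day window for the primary outcome.

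- **Start event.** Preferably the date the slip is issued, or the date of index treatment. Slip issue matches the existing denominator of women given a slip, and it covers women treated for a syndrome who may have no test-based diagnosis date.
- **Sensitivity analysis.** Report the 28-day outcome counted from diagnosis, with diagnosis defined.
- **Unchanged.** Keep the any-time outcome as secondary, and leave the denominator in the Statistical analysis section as it is. Counting women who never receive a slip as non-returns would be a separate change to the estimate and is not needed here.
- **Data.** Record the slip-issue date explicitly. The Randomisation and blinding section implies it, through the check of slip type against day of attendance, but does not state it.

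The cost is a few sentences, one recorded date, and slightly longer administrative follow-up for late-treated women. The main secondary outcome, days to attendance, would still start at diagnosis, and the protocol should say that this difference is intended.

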### Sample size calculations

As a trial embedded within a larger study, sample size calculations were not performed to power this trial. The main IPSAZ study has a target sample size of 1000 pregnant women, based on an estimated composite STI prevalence of 30%, a desired precision of 3%, an alpha of 0.05, and an additional 10% of participants to account for invalid test results
^
6,
25–
33
^.

From the initial pilot data from the IPSAZ study, we estimated a 30% prevalence of curable STIs and a recruitment rate of 5 participants per clinic day. For analysis, each clinic day will be considered as a unit of randomisation. It is therefore predicted that 300 index participants will receive partner notification slips, over 200 recruiting clinic days. This equates to 100 ‘clusters’ per arm, with an average of 1.5 participants per cluster.

The intra-cluster correlation coefficient (ICC) is assumed to be zero as the outcome is not expected to be more or less likely in participants having attended on the same day, compared to on different days. However, given the very small size of the clusters, even if the ICC was higher, it is unlikely to have a meaningful effect on the design effect size.

Initial data suggest that an estimated 30% of indexes have at least one partner returning for treatment. Assuming this, and an alpha of 0.05, a power of 0.8, an ICC of zero, 100 clusters per arm, and 1.5 participants per cluster, results in a minimum detectable odds ratio of 1.96 for the intervention (
Table 1). A higher ICC of 0.10 results in a minimum detectable odds ratio of 1.99.

**Table 1. T1:** Minimum detectable odds ratios for effect size of intervention, for differing proportions meeting the primary outcome in the control arm, assuming an alpha of 0.05, 100 clusters per arm, and 1.5 participants per cluster.

		ICC = 0.0		ICC = 0.1	
Sample size	Proportion meeting primary outcome in control arm	Smallest odds ratio detected at 80% power	Smallest odds ratio detected at 90% power	Smallest odds ratio detected at 80% power	Smallest odds ratio detected at 90% power
300	20%	2.09	2.33	2.13	2.37
	25%	2.01	2.22	2.04	2.27
	30%	1.96	2.17	1.99	2.21
	35%	1.93	2.13	1.96	2.17
	40%	1.92	2.12	1.95	2.16

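### The main secondary outcome, days to partner attendance, has no value for indexes whose partner never attends, so comparing arms on it as worded would not be a randomised comparison

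*Protocol article*

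**What the plan says.** The Outcomes section of the protocol article sets three outcomes on partner return.

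- The primary outcome is the "proportion of indexes with at least one partner who returns to the study site for partner services within 28 days of index diagnosis".
- A further secondary outcome is the same proportion without a day limit.
- Between these two stands the day count: "The main secondary outcome will be the number of days between index case diagnosis and the partner attending for partner services".

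The two proportions are taken over indexes, so an index without a returning partner counts as a failure. The day count names no population, no horizon and no rule for such an index.

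The Sample size calculations section shows how common that case will be: "Initial data suggest that an estimated 30% of indexes have at least one partner returning for treatment". It expects 300 indexes with slips, and its effect size "results in a minimum detectable odds ratio of 1.96 for the intervention".

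The Statistical analysis section commits to intention-to-treat. The only between-arm method it names is logistic regression with robust standard errors, which suits a yes/no outcome and not a number of days. The Proposed intervention section treats partners as lost to follow-up 28 days after treatment of the index. It does not tie that limit to the day count, and the starting point differs from the diagnosis date used for the primary outcome.

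**The concern.** Days to attendance can be observed only where attendance happens. Attendance comes after randomisation and is the event the incentive is meant to bring about. The attenders in the incentive arm would therefore be a mixture: partners who would have come anyway, and extra partners who came because of the money. The control arm has no counterpart to the second group.

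The protocol's Rationale makes such a difference plausible, because it expects the incentive to ease socioeconomic barriers, transport cost above all. Partners held back by cost may well attend at different times from those who were not.

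A contrast of days among attenders would then mix two things: any change in how fast a given partner comes, and the change in who comes. Neither its sign nor its size could be read as an effect of the incentive on speed. It would also sit badly with the stated intention-to-treat principle, since most indexes would drop out of it. This is the leading secondary outcome, so its result would probably be reported and discussed next to the primary one.

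**Working it through.** **1. Reproduce the plan's figure.** Inputs from Sample size calculations: 300 indexes, hence about 150 per arm at 1:1; control proportion 0.30; alpha 0.05 (two-sided); power 0.80; ICC 0.

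- Incentive proportion at odds ratio 1.96: 0.30 × 1.96 / (0.70 + 0.30 × 1.96) = 0.588 / 1.288 = 0.4565.
- The two-proportion normal formula with pooled variance, at 150 per arm, gives power 80.1% at this odds ratio. Solved for 80% power, it gives 1.958.
- With design effect 1 + 0.5 × 0.1 = 1.05 it gives 1.990, against the stated 1.99.

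The plan's figures reproduce, so 30% v 45.65% is a fair reading of its design effect.

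**2. How many indexes would have a value.**

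- Control: 150 × 0.30 = 45.
- Incentive: 150 × 0.4565 = 68.5.
- Total: 113.5 of 300 = 38%. About 187 (62%) have none.
- Incentive-arm attenders with no control counterpart, if nobody is deterred: 68.5 − 45 = 23.5, and 23.5 / 68.5 = 34%.

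**3. What an attenders-only comparison could show.** The documents give no timing, so everything in this step is assumed. In (a) to (d), partners who would come anyway follow an exponential distribution with parameter 7 days, truncated at 28. Its mean is 7 − 28e⁻⁴ / (1 − e⁻⁴) = 6.48. The incentive-arm mean is w × (mean of existing attenders) + (1 − w) × (mean of extra attenders), with w = 0.30 / 0.4565 = 0.657.

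- (a) Extra partners come uniformly on days 7 to 28 (mean 17.5): 0.657 × 6.48 + 0.343 × 17.5 = 10.3.
- (b) As (a), and existing attenders come 20% sooner (mean 5.18): 0.657 × 5.18 + 0.343 × 17.5 = 9.4.
- (c) Extra partners have the same timing as existing ones: 6.5.
- (d) Extra partners come uniformly on days 0 to 7 (mean 3.5): 0.657 × 6.48 + 0.343 × 3.5 = 5.5.
- (e) Constant hazards over all indexes, with hazard ratio ln(0.5435) / ln(0.70) = 1.71. The mean among attenders is 28 / (−ln S) − 28 S / (1 − S), with S the proportion not attending by day 28. Control: 78.5 − 65.3 = 13.2. Incentive: 45.9 − 33.3 = 12.6.

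**4. The same scenarios over all indexes.** Restricted mean time to day 28 is the sum of (proportion × mean days) over attenders plus 28 × (proportion not attending).

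- Control in (a) to (d): 0.30 × 6.48 + 0.70 × 28 = 21.5.
- Incentive in (a): 0.30 × 6.48 + 0.1565 × 17.5 + 0.5435 × 28 = 19.9.
- In (b), 5.18 replaces 6.48. In (c) and (d), 6.48 and 3.5 replace 17.5.
- In (e), (1 − S) × 28 / (−ln S): 0.30 × 78.5 = 23.6 and 0.4565 × 45.9 = 21.0.

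| Scenario (assumed) | Mean days among attenders, control v incentive | Restricted mean days, all indexes, control v incentive |
|---|---|---|
| (a) extra partners come late | 6.5 v 10.3 | 21.5 v 19.9 |
| (b) as (a), others 20% sooner | 6.5 v 9.4 | 21.5 v 19.5 |
| (c) same timing | 6.5 v 6.5 | 21.5 v 18.2 |
| (d) extra partners come early | 6.5 v 5.5 | 21.5 v 17.7 |
| (e) proportional hazards | 13.2 v 12.6 | 23.6 v 21.0 |

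Attendance is 30% v 45.65% in every row and nobody is delayed. The middle column nevertheless reads slower, slower, equal, faster and almost equal. The right-hand column favours the incentive throughout.

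**5. Power of an all-index analysis.** With 113.5 events and hazard ratio 1.71, Schoenfeld's formula gives √(113.5 / 4) × ln 1.71 − 1.96 = 0.90, that is about 81% power (proportional hazards and ICC 0 assumed).

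**The case against.** The strongest reply is that the article names a variable and not an analysis. Days from an origin to an event is also the plain-language way to describe a time-to-event outcome. Censoring rules and models are usually left to the analysis plan, which is not shown, and one that censored non-attenders would remove the problem. The unrestricted commitment to intention-to-treat and the linked slip identifiers are compatible with that.

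Part of this stands. A reader might infer that the trial plans to compare mean days among attenders only. The article does not say so, and silence on the model is not an error. What remains is the outcome definition, which belongs to the protocol. The neighbouring outcomes carry a denominator of indexes; this one does not, and read literally it drops most of them.

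Three other strong readings also fail.

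- **That the incentive will look slower.** The direction depends entirely on assumed timing, as the table shows.
- **That the comparison conditions on the primary outcome.** The day count has no 28-day limit, so it conditions on attendance at any time, which is close to the primary outcome but not the same.
- **That several attending partners per index make the outcome seriously ambiguous.** The Discussion cites survey data with under 1% of women reporting concurrent partners, or fewer than about 3 of 300 indexes if that rate applied here.

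It is also fair to say that a reader would see the attendance proportions beside the day count, and that an all-index measure overlaps with the primary outcome.

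**Conclusion.** The point holds in conditional form. As worded, the main secondary outcome is defined for about 30% of control indexes and, at the design odds ratio of 1.96, for about 38% of all indexes. If the arms are compared on it literally, the comparison is made within groups selected by an event the incentive is meant to change, so it is not randomised and its sign cannot be interpreted. The counts rest on the protocol's own 30% and 1.96. The sizes in days rest on assumed timings and show only that the sign is free to vary; they do not predict this trial's result. The primary outcome is not affected. The definition should be repaired before arms are compared, unless the analysis plan already covers all indexes, in which case the protocol wording should be brought into line with it.

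**What to change.** Redefine the main secondary outcome as time from index diagnosis, the same starting point as the primary outcome, to the first partner attendance, among all indexes given a PN slip, with non-attenders censored at day 28 from diagnosis. Compare arms with cumulative incidence curves and either a Cox model or restricted mean time to day 28, with standard errors clustered on clinic day. Report days among attenders by arm as description only, without a test. Taking the first attendance also settles the rare index with more than one attending partner.

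The cost is a change of wording in the protocol and the analysis plan. The slip identifiers already link each partner to an index, so no new data are needed. The small downside is that the all-index measure overlaps with the primary outcome and does not isolate speed among those who attend.
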